### **4.2 Blinding**

This study is an open-label study, and both participants and investigators will not be blinded to the study.

### **4.3 Intervention Group (LMWH + insulin group)**

In the LMWH + insulin group, a 4000 IU of LMWH sodium injection (enoxaparin) will be injected subcutaneously once every 12 hours for three days. Continuous usage of LMWH at prophylactic dosages will be considered for patients assessed to be at high-highest risk of venous thromboembolism and low bleeding risk, which was on chief physician's discretion.

For those with a glucose level > 11.1 mmol/L, patients will receive micropumps of insulin at 2 to 6 U/h, monitor blood glucose closely, to maintain the serum glucose levels between 7.8 and 10 mmol/L. When the glucose levels fall below 7.8 mmol/L, 6 U of insulin will be added to 500 mL of 5% glucose for intravenous infusion until the TG levels decrease to less than 5.65 mmol/L (500 mg/dL) or for a maximum duration of 5 days after randomization, whichever occurs first. For those with a glucose level ≤11.1 mmol/L, patients will receive 6 U of insulin with 500 mL of 5% glucose for intravenous, twice a day for 5 days, if hypoglycemia occurs, 5% dextrose change to 10% dextrose.

### **4.4 Control Group (insulin group)**

The insulin group received identical insulin therapy as described for the LMWH + insulin group.

### **4.5 Drug Withdrawal Standard**

When TG levels reach less than 500 mg/dL or at 5 days after enrollment, insulin will

be stopped and oral lipid-lowering drugs will be administered in the above two groups. If the blood glucose level is still greater than 11.1 mmol/L, insulin will be maintained to control the blood sugar. While LMWH administration was limited to 3 days (irrespective of triglyceride levels) in the LMWH + Insulin Group. However, LMWH (4000 IU every 12 hours for 7-10 days) was administered as venous thromboembolism (VTE) prophylaxis in high-risk patients (Padua score  $\geq 4$ ), and with low bleeding risk in both groups.

#### **4.6 General Treatment Regimen**

Early medical treatments include fasting for 48 hours, fluid resuscitation and analgesia. Patients will be offered intensive care after organ failure. Antibiotics were given after clinically suspected or confirmed infection. Mild HTGP patients without severe abdominal pain or vomiting after admission will be orally fed low-fat food. Moderate and severe HTGP patients who cannot tolerate oral feeding will be given a nasojejunal nutrition tube for enteral nutrition. Enteral nutrition used by nasal jejunal tube is generally started at 72 hours after AP onset with a low dose of peptison (20 mL/h). The nutritional goal is achieved after 1 week if the tolerance of enteral nutrition feeding is gradually increased. The patient would reduce the dose of enteral nutrition, and the enteral nutrition feeding would generally be stopped 1 month later. Patients with serum TG levels of greater than 500 mg/dL will not be given enteral nutrient solutions containing fatty milk. If the TG levels remain at 250 mg/dL at 5 days after enrollment, oral lipid-lowering drugs will be administered, and 200 mg/d of fenofibrate (Recipharma, Fontaine, France) is the first choice for the long-term control of TG levels. Serum TG levels will be controlled with a combination of statin lipid-lowering drugs if they cannot be controlled by fibrates alone.

[figure not shown]

**Figure 1** Flow chart of the study. AP, acute pancreatitis; TG, triglyceride; LMWH, low-molecular-weight heparin; ITT, intention to treat; PP, per-protocol.

## 5 OUTCOMES

### 5.1 Primary endpoint

The primary endpoint is a composite of new-onset organ failure and mortality within one month after randomization, excluding events occurring within 24 hours before randomization. Organ failure includes respiratory failure, renal failure, and circulatory failure, which is defined as a score of 2 or more using the modified Marshall scoring system^28.

### 5.2 Secondary endpoints

All the endpoints are assessed and collected within one month after randomization including 1) New-onset organ failure including respiratory failure, renal failure, and circulatory failure; 2) Mortality; 3) The time to achieve the TG goal of <5.65 mmol/L, which will be detected using a fully automated blood biochemistry analyzer; 4) New-onset SIRS; 5) Necrotizing pancreatitis; 6) Infected pancreatic necrosis; 7) Sepsis;

8) Pulmonary infection; 9) Vein thrombosis; 10 ) Pseudoaneurysm; 11) Sinistral portal hypertension; 12) Abdominal compartment syndrome; 13) Cerebral hemorrhage; 14) Demand for mechanical ventilation; 15) Renal replacement therapy; 16) Percutaneous drainage of ascites; 17) Drainage of pancreatic necrosis; 18) Debridement of pancreatic necrosis; 19) Vascular interventional therapy; 20) Duration of intensive care unit stay; 21) Length of hospital stay; 22) Hospital costs.

### 5.3 Safety endpoints

Safety outcomes include the new-onset bleeding, the rebound of serum TG, and drug-related adverse events (AEs). The new-onset bleeding is defined as new-onset abdominal or gastrointestinal bleeding occurring within two weeks after randomization. The rebound of TG is indicated by an increase in TG levels after prolonged use of heparin, with TG levels measured five days after randomization surpassing the TG levels measured within three days after randomization.

|                     | STUDY PERIOD |            |                 |       |       |       |       |           |
|---------------------|--------------|------------|-----------------|-------|-------|-------|-------|-----------|
|                     | Enrolment    | Allocation | Post-allocation |       |       |       |       | Close-out |
| TIMEPOINT           | Admission    | Day 0      | Day 1           | Day 2 | Day 3 | Day 4 | Day 5 | Day 28    |
| ENROLMENT           |              |            |                 |       |       |       |       |           |
| Eligibility screen  | X            |            |                 |       |       |       |       |           |
| Informed consent    | X            |            |                 |       |       |       |       |           |
| Allocation          |              | X          |                 |       |       |       |       |           |
| INTERVENTION        |              |            |                 |       |       |       |       |           |
| Two groups          |              |            | X               | X     | X     | X     | X     |           |
| ASSESSMENTS         |              |            |                 |       |       |       |       |           |
| Baseline variables  | X            | X          |                 |       |       |       |       |           |
| Primary endpoint    |              |            |                 |       |       |       |       | X         |
| Secondary endpoints |              |            | X               | X     | X     | X     | X     | X         |
| Safety endpoints    |              |            | X               | X     | X     | X     | X     | X         |

**Figure 2** The schedule of enrolment, interventions, and assessments of the study.

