| Duration of Treatment | Three days for LMWH.                                                                                                                                                                                                                                                                                                                                                                                                                                                                                                                                                                                                                                                                                                                                                                  |
| Follow-up             | All participants will be followed for a total of one month.                                                                                                                                                                                                                                                                                                                                                                                                                                                                                                                                                                                                                                                                                                                           |
| Informed consent      | Written informed consent will be obtained from all participants or their legal representatives.                                                                                                                                                                                                                                                                                                                                                                                                                                                                                                                                                                                                                                                                                       |

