### **9.3 Safety**

Insulin with or without heparin is regarded as safe therapy approach in routine clinical settings. Given the known safety endpoints mentioned in the Outcomes section and the absence of unknown drugs or therapies in the study, it is not anticipated that any further AEs or serious AEs would occur or be attributable to the

intervention during the trial. Throughout this trial, the IDMC will examine safety variables every six months. Investigators will also report serious AEs on a separate form, which must be sent to the IDMC and the medical ethics committee of the FAHNU.

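### The between-arm safety comparison leaves out some bleeding and all-cause serious adverse events, and its two-week bleeding window does not match the Day 28 safety assessment

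*Protocol*

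**What the plan says.** The synopsis and section 2 give the objective as comparing both efficacy and safety. Section 5.3 names three safety outcomes: new-onset bleeding, rebound of serum triglyceride, and adverse events that are drug-related. The first is restricted by site and by time: "The new-onset bleeding is defined as new-onset abdominal or gastrointestinal bleeding occurring within two weeks after randomization".

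Other parts of the protocol bear on this:

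- **Follow-up.** The synopsis states: "All participants will be followed for a total of one month". Figure 2 (in section 5.3) marks safety endpoints on Days 1 to 5 and again at Day 28.
- **Secondary endpoints.** Section 5.2 opens with "All the endpoints are assessed and collected within one month after randomization". Its list includes cerebral haemorrhage (item 13), pseudoaneurysm, vascular interventional therapy and mortality.
- **Masking.** Section 4.2: "This study is an open-label study, and both participants and investigators will not be blinded to the study". No section describes blinded or independent adjudication of bleeding or of drug-relatedness, and none names who judges relatedness.
- **LMWH exposure.** Section 4.5 limits the assigned course to three days. It also provides prophylaxis for high-risk patients with low bleeding risk in both groups ("4000 IU every 12 hours for 7-10 days"), with no start day stated.
- **SAEs.** Section 9.3 has investigators send SAEs on a separate form to the monitoring committee and the ethics committee, with no condition on attribution. It also says that "it is not anticipated that any further AEs or serious AEs would occur".
- **Analysis.** Section 8.2 compares the secondary endpoints and the safety outcomes between arms, with all randomised patients as the safety population.

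**The concern.** Bleeding is the expected harm of the agent under test, and the protocol treats it so: the introduction raises pancreatic haemorrhage, and section 10 cites haemorrhage risk as a reason to exclude patients with acute renal failure. The definition in 5.3 is a fixed rule, not a detail left open for a later document. Followed as written, it means that no single comparison counts all bleeding by arm.

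The adverse-event outcome has a different weakness. In an open-label trial, whether an event is called drug-related can depend on knowing which drugs the patient received. Every patient in one arm is assigned LMWH, while in the other only those given prophylaxis receive it. The drugs to which an event can be attributed therefore differ by arm.

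The stake is the safety half of the objective. The trial could report no excess of bleeding while some relevant events lie outside the outcomes it compares. Widening the definition once results by arm are known would look post hoc.

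**Working it through.** The protocol gives no bleeding rate, safety power or safety margin, so there is no figure to reproduce. The check sets the definitions side by side, does the window arithmetic, and adds one illustration on assumed rates.

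**1. Where each type of event enters the comparison specified in 8.2**

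| Event | Route into the comparison |
|---|---|
| Abdominal or GI bleed, Day 14 or earlier | Bleeding outcome (5.3) |
| Abdominal or GI bleed after Day 14 | Only as a drug-related AE, if so attributed |
| Cerebral haemorrhage, to one month | Secondary endpoint 13 (5.2) |
| Bleed at another site (e.g. urinary, airway, injection site) | Only as a drug-related AE, if so attributed |
| SAE of any cause | Reported under 9.3, but not a listed outcome, so no comparison by arm is specified |
| Non-serious AE not attributed to drug | None, unless it is a listed endpoint |

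**2. Windows**

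- Share of follow-up covered, taking Day 28 as close-out: 14 / 28 = 50%. Days 15 to 28 are outside the bleeding outcome.
- Assigned LMWH is three days, so the window runs 14 − 3 = 11 days past it.
- If the 7-10 day prophylaxis followed the assigned course directly, it would end at 3 + 7 = Day 10 to 3 + 10 = Day 13, inside the window. The start day is not stated, so exposure after Day 14 is possible but cannot be derived from the document.
- Figure 2 shows no visit between Day 5 and Day 28. The two-week cut therefore saves no scheduled visit.

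**3. Illustration of what an incomplete count costs**

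Assumptions, none of them from the protocol: all-site bleeding rates p₁ (insulin) and p₂ (LMWH + insulin), and a share f of all bleeds that meets the definition, equal in both arms. The 270 per arm comes from section 8.1; alpha is two-sided 0.05. With observed rates q₁ = f·p₁ and q₂ = f·p₂, and q̄ their mean,

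power = Φ{ [ (q₂ − q₁) − 1.96·√(2q̄(1 − q̄)/270) ] / √( [q₁(1 − q₁) + q₂(1 − q₂)]/270 ) }.

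For 2% vs 6% and f = 1: (0.04 − 1.96 × 0.01687) / 0.01678 = 0.41, and Φ(0.41) ≈ 0.66.

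| Assumed all-site rates | f = 1 | f = 0.8 | f = 0.5 |
|---|---|---|---|
| 2% vs 6% | 66% | 56% | 38% |
| 3% vs 8% | 72% | 62% | 43% |

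The expected excess that is counted, 270 × (p₂ − p₁) × f, falls from 10.8 to 8.6 to 5.4 patients in the first row.

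**The case against.** The case for leaving the outcome alone has real strength.

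- **Cerebral haemorrhage is not lost.** It is collected to one month and compared between arms under 8.2. Placing it among the secondary endpoints is a matter of classification. This stands. A reader might infer that 5.3 holds the only comparison of harm, but the documents do not support that: 5.3 has two further safety outcomes, and 5.2 adds several complications and mortality.
- **Bleeds elsewhere have a route.** One attributed to drug is a drug-related AE, and a serious one reaches the monitoring committee whatever the attribution. This stands too, so it would be wrong to say that other sites count nowhere. The low expectation of further events in 9.3 does not restrict reporting. Oversight during the trial is not, however, the comparison by arm that 8.2 specifies.
- **The window fits the randomised exposure.** It outlasts the assigned course by 11 days, and prophylaxis is open to both groups. This largely stands. A reader might infer that on-drug bleeding must fall outside the window, but that needs a late start of prophylaxis, which the document does not give. Day 28 in Figure 2 may also only mark collection at close-out, and the one-month sentence sits under the secondary endpoints. The mismatch is therefore something to reconcile, not proof of error.
- **Relatedness.** The protocol does not say that unblinded staff judge it; that is an inference from the open-label design. Insulin is a study drug in both arms and controls may receive LMWH, so control patients can have drug-related events. What remains is that the filter is not neutral between arms and that no safeguard is described.
- **Grading of bleeds** can properly be left to an analysis plan. Accepted.

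**Conclusion.** The concern holds in limited form and should be fixed. It does not touch the primary endpoint.

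The specified safety comparison omits three things: bleeds that are neither abdominal, gastrointestinal nor cerebral and are not attributed to drug; abdominal or gastrointestinal bleeds after Day 14, unless they enter as drug-related AEs; and all-cause SAEs by arm. The bleeding outcome covers half of the 28 days and does not match the one-month follow-up or the Day 28 safety assessment in Figure 2.

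These conclusions rest on the text of 5.2, 5.3, 8.2 and 9.3. How many events are affected cannot be derived from the document. The loss of power shown above is illustrative and depends on the assumed rates and shares. The site restriction and the attribution filter are the stronger parts; the window is mainly an inconsistency to resolve.

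**What to change.** In section 5.3:

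1. Add as a safety outcome, compared by arm, any new-onset bleeding at any site, cerebral haemorrhage included, from randomisation to Day 28.
2. Keep the two-week abdominal or gastrointestinal definition as a secondary cut. This also settles the mismatch with Figure 2.
3. Add a comparison by arm of all SAEs already reported under 9.3, regardless of attribution.

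A severity grade for bleeding is optional and can go in the analysis plan. The changes should be made before results by arm are known.

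The cost is small. Patients are already followed to Day 28, Figure 2 already marks safety endpoints there, and SAEs are already recorded. A few more non-specific events would have to be recorded and tabulated. The case report form is not shown, so the exact number of added fields cannot be given. No treatment rule needs to change.

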## 6 ETHICS AND DISSMINATION

### 6.1 Guiding principles

This study is to be performed in accordance with the ethical principles of the

Declaration of Helsinki (June 1964 and amended 1975, 1983, 1989, 1996, 2000, 2008, 2013 and Note of Clarification 2002 and 2004), China GCP Notes for Guidance on Good Clinical Practice (GCP).

## **6.2 Ethical considerations**

Ethical review procedure: All subsites engaged in this study must be reviewed and approved by the ethics committee of the hospital before study initiation. The amendment of the study protocol and informed consent form should be submitted to the ethics committee for re-review and re-approval;

Ethics committee review of the sponsor's organization: Prior to study initiation, the principal investigator should submit the investigator's brochure, study protocol, informed consent form, CRF, and qualifications and resumes of the investigators, and other major study materials to the ethics committee of the study sponsor's organization for review and approval;

Ethics committee review of the subsite organization: The principal investigator of each subsite should submit the approval letter issued by ethics committee of the sponsor's organization, the investigator's brochure, study protocol, informed consent form, CRF, qualifications and resumes of the principal investigator from the subsite, and other study data to the ethics committee of the hospital for review and approval;

When reviewing and approving study documents, the ethics committee must confirm the study title and indicate the version number, version date and review date of the reviewed study documents.

## **6.3 Informed consent form**

The investigator must inform the subject or his/her legal representative of the information about the study in both oral and written ways. The subjects or their legal representatives have the right to know the detailed information about this study.

The informed consent form (ICF) must be reviewed and approved by the ethics committee. If necessary, the investigator is responsible for explaining the contents of the ICF to the subject in a manner that the subject can understand. The subject or his/her legal representative should have sufficient time to read and understand the

ICF before signing it.

The ICF must be signed and dated by the subject or his/her legal representative. The signed ICF should be kept separately by the investigator and the subject, and the investigator should keep the original copy on file for monitoring and audit.

#### **6.4 Privacy Protection of Subjects**

The investigator takes the responsibility to maintain the anonymity of subjects and keep documents showing the identity of subjects strictly confidential. In CRFs or other study documents, subjects can only be identified with codes. The investigator must properly maintain a screening form that records the subject code, name, and home address.

#### **6.5 Dissemination Policy**

A writing committee will be formed to review and publish the data from the study. This committee will consist of the Steering Committee and a subset of investigators. The writing committee will write/review all drafts of abstracts and full-length manuscripts and will choose the appropriate journal (for manuscripts) or meeting (for abstracts) for submission.

The steering committee commits that when the study is completed, the data from this study will be published, regardless of the outcome of the study. All information concerning the trial supplied to the investigators by the steering committee and not previously published is considered confidential and shall remain the sole property of the steering committee. The investigator agrees to use this information only in accomplishing the study and will not use it or the data generated from the study for other purposes without first obtaining written authorization from the steering committee.

### **7 DATA MANAGEMENT**

All data will be collected prospectively using paper-based case report forms (CRFs). Data entry was performed by the nominated investigators (one or two in each participating center). The quality of CRFs was regularly (almost 6 months) inspected by independent investigators to ensure accuracy, completeness and legibility. Any

missing, implausible, or inconsistent data recorded in the CRFs were sent back to investigators to review and amend if necessary and before clean file status was declared.

An electronic database (EpiData Entry, <https://www.epidata.dk/>) was used for data double entry and validation. All data stored in the electronic database were de-identified to ensure patient confidentiality. Training for data entry and the use of the EpiData software was performed by the lead site (FAHNU), which also assumed responsibility for data safety, privacy and quality.

## **8 STATISTICAL CONSIDERATIONS**

### **8.1 Sample size**

This study is designed as a superiority trial, and the sample size is calculated based on data from previous clinical studies. The occurrence rate of the new-onset organ failure and/or mortality of LMWH combined with insulin in HTGP patients is 8.3%, whereas that for treatment with insulin alone in HTGP patients is 17.86%. We estimate that a sample size of 490 participants will provide 80% power at a two-sided alpha level of 0.05 to detect a 9.56% reduction in the composite primary endpoint. Given an attrition rate of 10%, we plan to randomize 540 patients in total (270 per group). The sample size was calculated using PASS software (PASS V.11, NCSS software, Kaysville, USA).

